#### Sample size

The sample size calculation for this study is based on a feasibility study of implementing The Drug Burden Index Calculator© report into the HMR service [25]. In the feasibility study, 18 pharmacists recruited 100 patients (average cluster size 5.6) where 25 (25%) patients had a reduction in their DBI score, 7 (7%) patients had an increase in their DBI score, whilst the remaining 68 (68%) had no change in DBI score. The estimated intra-cluster correlation (ICC) was 0.07. With a sample size of 500 participants, we will have 80% power to detect a 10% difference between the intervention and comparison groups, corresponding to 20% of participants in the intervention group and 10% of participants in the comparison group having a reduction in DBI, assuming a 5% significance level (two-sided) and an Intra-cluster Correlation Coefficient (ICC) = 0.07. This corresponds to a relative reduction of 2, therefore we will be powered to detect a difference corresponding to twice the reduction in the intervention compared to the control.

As of March 2017, there were 2374 general registered ACPs practising in Australia. To reach the estimated clustered sample size of 500 patients, approximately 120 pharmacists will need to be recruited, 60 pharmacist participants in each of the intervention and comparison groups (allowing for 20% dropout rate – estimate based on the previous study [25]). Each ACP will be required to recruit 5–10 participants to achieve an average of 5 patients per ACP (total of 500 patients).

Using published national statistics, we estimate that 10–31% (*n* = 50–155) of recruited patients will have a diagnosis of dementia and subgroup analyses is planned on these participants [10].

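### The pharmacist target yields 480 patients, not the 500 behind the 80% power, because the 20% dropout allowance was multiplied on rather than divided out; the effect on power is small

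*Protocol article*

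**What the plan says.** All the figures are in the Sample size section of the protocol article.

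- Power and total: "With a sample size of 500 participants, we will have 80% power to detect a 10% difference".
- Effect: "20% of participants in the intervention group and 10% of participants in the comparison group having a reduction in DBI".
- Error rate and clustering: the test is two-sided at 5%, with "Intra-cluster Correlation Coefficient (ICC) = 0.07".
- Clusters and loss: "approximately 120 pharmacists will need to be recruited, 60 pharmacist participants in each of the intervention and comparison groups (allowing for 20% dropout rate"). The 20% is taken from the feasibility study.
- Patients per cluster: "Each ACP will be required to recruit 5–10 participants to achieve an average of 5 patients per ACP (total of 500 patients").

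The section also reports the feasibility study behind the ICC: 18 pharmacists and 100 patients, a mean of 5.6 each. It does not say whether the 20% is loss of pharmacists or of patients, or whether the average of 5 is counted before or after that loss.

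**The concern.** The number of pharmacists, the dropout rate, the average per pharmacist and the patient total are linked by one multiplication, and the four stated values do not satisfy it. The total of 500 is what supports the power claim for the primary outcome, and it carries no reserve: the standard formula asks for 502 to 509 patients. A recruitment target that falls short of 500 on its own assumptions therefore takes power below the stated level.

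The rule for each pharmacist adds to the uncertainty. If everyone must recruit at least 5, the mean equals 5 only when nobody exceeds the minimum. Cluster size also sets the design effect, so the intended mean should be clear.

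**Working it through.** **Inputs (all from the Sample size section).** Two-sided 5%; 20% versus 10%; ICC 0.07; mean cluster size m = 5; 500 patients, 250 per arm; 120 pharmacists; 20% dropout.

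**Step 1. Reproduce the stated size.**
- Design effect: 1 + (5 − 1) × 0.07 = 1.28.
- Unpooled variance, per arm before clustering: (1.96 + 0.842)² × (0.16 + 0.09) / 0.10² = 196.2. Total: 2 × 196.2 × 1.28 = 502.
- Pooled variance: 199 per arm. Total: 2 × 199 × 1.28 = 509.

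Both are within 2% of 500, so the stated size reproduces.

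**Step 2. Power at 500.** With n per arm, the unpooled form is Φ(0.10 / √(0.25 × DE / n) − 1.96).
- n = 250, DE = 1.28: Φ(2.795 − 1.96) = 79.8%. The pooled form gives 79.3%.

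**Step 3. Number of pharmacists.**
- Contributing pharmacists needed: 500 / 5 = 100.
- Stated target: 120 = 100 × 1.2.
- Allowance for 20% loss: 100 / (1 − 0.20) = 125, or 126 (63 per arm) with equal arms.

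**Step 4. What 120 yields at an average of 5.**
- Loss of pharmacists: 120 × 0.8 = 96, and 96 × 5 = 480.
- Loss of patients: 120 × 5 = 600, and 600 × 0.8 = 480.

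Either way the shortfall is 20 patients, or 4%. If the average of 5 were counted after patient loss with all 120 pharmacists contributing, the total would be 120 × 5 = 600, which does not match 500 either.

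**Step 5. Power at 480 with 5 per pharmacist (96 clusters).**
- n = 240, DE = 1.28: Φ(2.739 − 1.96) = 78.2% unpooled, 77.6% pooled. The loss against Step 2 is 1.6 to 1.7 points.

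**Step 6. Sensitivity to the reading.**

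| Reading | Patients | Design effect | Power (pooled to unpooled) |
|---|---|---|---|
| 100 pharmacists × 5 (as stated) | 500 | 1.280 | 79.3 to 79.8% |
| 96 × 5 | 480 | 1.280 | 77.6 to 78.2% |
| 120 × 4 (20% patient loss, spread evenly) | 480 | 1.210 | 79.9 to 80.4% |
| 96 × 5.21 | 500 | 1.295 | 78.8 to 79.4% |
| 96 × 5.6 (feasibility mean) | 538 | 1.322 | 80.9 to 81.4% |

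The mean that 96 pharmacists need to reach 500 is 500 / 96 = 5.21. The third row shows why the unit of loss matters: the patient total is the same as in the second row, but the clusters are smaller and power is essentially kept.

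**The case against.** The strongest reply is that 480 is a floor. The same paragraph asks for 5 to 10 patients from each pharmacist, so 96 retained pharmacists would give between 480 and 960. They need a mean of only 5.21 to reach 500, and at the feasibility mean of 5.6 they would exceed it. Pharmacists who leave may also contribute some patients first: 20 patients across the 24 who leave would close the gap. The target is worded as approximate, and fewer than two power points are involved.

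Most of this stands, and it limits the size of the point. It does not remove it. The article states the average as 5, and at that average the sum is 480. The word for approximate does not explain the figure, since 120 is exactly what multiplying by 1.2 gives.

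Three stronger readings are tempting, and the article does not support them.

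- A reader might infer that the 5 to 10 rule contradicts the average of 5. It is a tension that meets at the minimum. It can be read as a target per pharmacist with a lower realised average after under-recruitment or loss, although the article does not say so. The Stage II section on recruitment of participants uses 5 to 10 for patients who have completed follow-up, which sits less easily with that reading.
- A reader might infer that larger clusters cut power sharply. That requires holding the total at 500 while the mean rises, so that at 7.5 each only 500 / 7.5 ≈ 67 pharmacists contribute. Nothing in the article plans for so few. With 96 pharmacists, means of 7.5 and 10 give 720 and 960 patients and about 88% and 93% power.
- A reader might infer that the end of recruitment is undefined. The total of 500 is stated more than once as the target.

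**Conclusion.** The point holds as an arithmetic slip of modest size. With 120 pharmacists, 20% dropout and an average of 5, the yield is 480 patients and not 500. Power is then about 78% (77.6 to 78.2%) against 79.3 to 79.8% at 500.

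That power figure assumes that whole pharmacists are lost, that the 96 who remain average exactly 5, that clusters are equal in size, and that every patient counted has the 3-month outcome. If the 20% is instead spread evenly over patients, the total is still 480 but power stays near 80%.

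The stated 500 and 80% are themselves correctly derived to within rounding. A reader should not conclude that the trial is seriously underpowered or that 500 is out of reach. The finding is that the stated figures do not agree with one another and that the wording about patients per pharmacist is loose.

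**What to change.** Restate the Sample size paragraph so that the figures agree, in one of three ways:

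1. Keep 120 pharmacists, and state that 20% pharmacist dropout at 5 patients each leaves 96 pharmacists, about 480 patients and about 78% power.
2. Keep 500 patients at 5 each, and raise the target to about 125 pharmacists, or 126 with equal arms.
3. Keep 120 pharmacists and 500 patients, and state the required mean as at least 5.2 analysed patients per retained pharmacist, with about 79% power.

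In each case, say whether the 20% is loss of pharmacists or of patients, and whether the average of 5 is before or after that loss. Reword the 5 to 10 requirement so that its relation to the average is explicit, for example as a target per pharmacist with a separately stated expected mean after loss.

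The first and third options cost only rewording and a stated power one or two points lower. The second costs five or six more pharmacists. None changes the design or the analysis.

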#### Statistical analyses

The primary analyses will be conducted using an ‘intention-to-treat’ approach and will be reported according to the guidelines of the Consolidated Standards of Reporting Trials (CONSORT) 2010 statement. Descriptive statistics (means and proportions) will be used to report the demographics of the study populations (ACPs and patient participants) at baseline. Binary continuous and count outcomes will be analysed using logistic, linear and negative binomial regression models, respectively. All models will include a covariate for the intervention group, with a random effect for the clusters (ACPs). Analyses will provide an estimate of the difference between groups, 95% confidence intervals (CI) and *p*-values. All statistical tests will be two-tailed, and p-values of < 0.05 will be deemed statistically significant. Appropriate model checking will be conducted. The statistician performing the data analysis will be blinded to the identity of each treatment group.

Secondary analyses will include:
Where appropriate, to conduct further adjusted analyses, covariates will be included for the patients’ baseline value (for that outcome) and any baseline characteristic for which there is evidence of imbalance between intervention and comparison groups;A subgroup analysis for people living with dementia;For clinical outcomes, assessments of associations between change in DBI or a deprescribing of a medication, using the same statistical methods as described above, but with the intervention group removed from the model and replaced by change in DBI or deprescribing of medication;Association between rPATD and deprescribing in overall patient population.

To analyse the responses to the rPATD questionnaire, factor scores will be created for each of the 4 factors (appropriateness, burden, concerns about stopping and involvement) as previously described [34]. Likert responses to the global question ‘I would be willing to stop one or more of my medications if my doctor said it was possible’ will be dichotomised into those that agree (strongly agree and agree) and those that are unsure/disagree (unsure, disagree, strongly disagree). Factor scores and responses to the global questions will be compared to deprescribing outcomes (DBI and prevalence of deprescribing) using Mann-Whitney and χ^2^ tests.

To analyse the free-text goals of care for patients (or carers) in the intervention arm (entered into G-MEDSS), the data will be transferred to NVivo qualitative data analysis software (QSR International Pty Ltd. Version 12, 2018) and analysed thematically to assess the goals of care that patients have for their medications and clinical conditions. All goals will be grouped into type of goal (health-related or medication-related) by two investigators, and differences will be discussed until consensus is reached.

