##### Recruitment of older people

ACPs who are enrolled in the study and have completed the training to participate in the study (see ‘*Study procedure: training’)* will then screen and recruit people living with and without dementia, who are sequentially referred to them for a HMR. Eligibility for individual people living with and without a diagnosis of dementia include: aged 65 years and older who can speak English, are eligible for a HMR, and are able to provide informed written consent (patient or carer).

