##### Randomisation and blinding

ACPs will be randomised to the intervention or comparison groups after the ACPs volunteer, eligibility is checked, and consent is given to participate in the study. An online random number generator will be used to formulate a data sheet of ACP allocations to either the intervention or comparison groups [41]. ACPs and patients will not be blinded to the study group, however ACPs will be advised to not communicate with other enrolled ACPs about the study.

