#### Outcomes and follow-up

The primary outcome will be any reduction of anticholinergic and/or sedative medication use, as measured by DBI, between baseline and 3-months (binary outcome). Previous studies consistently observe an association between increasing DBI and impaired physical function [29]. The degree of exposure that results in a clinically significant change has been estimated to be a difference in DBI of approximately 0.5 [44]. Our previous study found that DBI is reduced in usual care HMR in 8.9% of patients by a median value of 0.28 [45], and an increase in this proportion by 10% was seen as a clinically meaningful effect on a population level. It was not feasible to power the study to primarily investigate impact on multifactorial measures of physical function.

Secondary outcomes will include:
Recommendations to reduce anticholinergic and or sedative medications as measured by DBI in the HMR report and/or the G-MEDSS report;Prevalence of deprescribing (cessation and/or dose reduction) any medicationChanges in clinical outcomes (physical function, cognitive function, falls, and institutionalisation)Changes in patient process outcomes (medication adherence and physician visits)Mortality at 3-monthsA subgroup analysis (of the above outcomes) for people living with and without dementia

All ACPs will be required to collect additional information of their HMR recipients at baseline (during HMR interview) and at a 3-month follow-up visit. The 3-month follow-up has been added exclusively to this study for the purposes of data collection as the HMR process (usual care) does not involve a follow-up visit. The following outcomes will be assessed of the patient participants enrolled in the study: medication adherence, cognitive impairment, functional status, falls, institutionalisation and the number of physician visits. Mortality data will be captured by the ACP participants at 3-month follow-up (Table 1).

**Table 1 Tab1:** Patient participant data to be collected during the study

	Measure (s)	Baseline^a^	3-months
Demographics			
Age		✓	
Sex		✓	
Ethnicity		✓	
Marital Status		✓	
Education Status		✓	
Geographic remoteness/locality	PhARIA	✓	
Medication Profile			
Current medication list (prescribed, OTC and complementary, regular or PRN)		✓	
Changes to medication list (e.g. additions, cessations, ↑↓dose)			✓
Ceased medications		✓	✓
Adherence	MGL	✓	✓
Attitudes towards deprescribing^b^	rPATD, rPATDCog	✓	
Anticholinergic and sedative burden	DBI	✓	✓

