### Limitations

There are several anticipated limitations within this study. Inherent biases in the sample population of ACPs and patients may affect the results of the study. ACPs usually work independently, therefore it is difficult to recruit ‘clinics’ of ACPs, similar to other cluster-randomised trials that involve general practice clinics. ACPs are also not blinded to the study group, therefore ACPs in the comparison arm may change their behaviour or clinical practice and this may not be reflective of true usual practice. On the other hand, ACPs in the intervention arm may recruit ‘clinically interesting’ patients that may ‘benefit’ from the intervention. To account for and to try to minimise these biases, all ACPs enrolled in the study will be required to undergo training (outlined above). The study is primarily powered to assess whether the intervention will reduce anticholinergic and sedative medication exposure, measured using DBI, after 3 months. It is not powered to assess differences in clinical outcomes, such as physical and cognitive function, even though this data will be captured. Therefore, we may not be able to detect a difference between the intervention and control groups regarding these clinical outcomes. The study will not collect quality of life measures for patients enrolled in the study or economic data on the impact of the intervention.

Regarding the process evaluation, the perspectives of the GPs will not be assessed. This may limit the interpretation of implementation of the intervention in the study and in clinical practice.

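### The primary model leaves out baseline DBI, although patients with DBI 0 cannot have the outcome and unblinded pharmacists recruit after allocation

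*Protocol article*

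**What the plan says.** - **Outcome.** Outcomes and follow-up defines the primary outcome as "any reduction of anticholinergic and/or sedative medication use, as measured by DBI, between baseline and 3-months (binary outcome").
- **Eligibility.** Recruitment of older people asks that patients be "aged 65 years and older who can speak English, are eligible for a HMR, and are able to provide informed written consent" (by patient or carer). It sets no minimum DBI.
- **Order of events.** Under Randomisation and blinding, "ACPs will be randomised to the intervention or comparison groups after the ACPs volunteer, eligibility is checked, and consent is given". That section also says that neither ACPs nor patients are blinded. Training differs by arm, and only trained ACPs go on to screen, invite and consent patients.
- **Foreseen selection.** Limitations says "ACPs in the intervention arm may recruit" patients whom they find clinically interesting and who may benefit. Training of all ACPs is the remedy named there.
- **Model.** Statistical analyses fixes the terms: "All models will include a covariate for the intervention group, with a random effect for the clusters (ACPs").
- **Adjustment.** This is listed under secondary analyses: "Where appropriate, to conduct further adjusted analyses, covariates will be included for the patients’ baseline value (for that outcome"), together with "any baseline characteristic for which there is evidence of imbalance between intervention and comparison groups".
- **Availability.** Table 1 has DBI collected at baseline, at the HMR interview, in both arms.

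**The concern.** DBI measures exposure to anticholinergic and sedative medicines, so a patient who takes none is a certain non-responder. The event rate in an arm is therefore the product of two quantities: the share of its patients with DBI above 0, and the chance of a reduction among them. G-MEDSS can act only on the second. The unadjusted model attributes a difference in either to the intervention.

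Randomising ACPs does not protect the first quantity, because patients enter later through someone who knows the arm. If intervention ACPs enrol more exposed patients, the primary analysis can show a benefit where there is none. The planned secondary adjustment is a weak safeguard for three reasons. It does not carry the primary conclusion. It is conditional, with further covariates chosen after looking at imbalance. And a baseline value for the outcome has no clear meaning when the outcome is itself a yes/no change, so the text does not plainly commit to baseline DBI.

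**Working it through.** **1. The plan's own sample size.** Inputs from Sample size: 20% v 10%, two-sided 5%, 80% power, ICC 0.07, 5 patients per ACP, 500 patients.

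- Pooled-variance formula: n = [1.960·√(2·0.15·0.85) + 0.842·√(0.2·0.8 + 0.1·0.9)]² / 0.10² = 199 per arm.
- Design effect: 1 + (5 − 1)·0.07 = 1.28. Total: 2·199·1.28 = 509 (502 with unpooled variance).
- Power with 250 per arm: the effective n is 250/1.28 = 195.3, which gives 79.3%.

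The stated 500 and 80% reproduce for the planned unadjusted model.

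**2. Assumption.** The documents do not give the share of patients with DBI above 0. In the feasibility study 25% had a reduction, so at least that share was exposed; 68% had no change, but how many of them had DBI 0 is not reported. I assume 60% in the comparison arm and vary it from 50% to 80%. The differences between arms are also assumed scenarios.

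**3. Bias with no treatment effect.** A 10% overall rate with 60% exposed means 0.10/0.60 = 16.7% among the exposed. Apply the same 16.7% to the intervention arm:

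- 70% exposed: 0.70·0.167 = 11.7%, a false difference of 1.7 points.
- 80% exposed: 0.80·0.167 = 13.3%, a false difference of 3.3 points, one third of the 10-point target.

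**4. False-positive rate of the unadjusted comparison.** Effective n is 195.3 per arm. SE₀ is the pooled standard error, SE₁ the unpooled one, and d the false difference. The chance of a significant result favouring G-MEDSS is P(Z > (1.96·SE₀ − d)/SE₁).

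- 80% v 60%: (1.96·0.0325 − 0.0333)/0.0324 = 0.94, so 17.5%. The opposite tail adds 0.1 points: 17.6%.
- 70% v 60%: (1.96·0.0315 − 0.0167)/0.0314 = 1.43, so 7.6%. The opposite tail adds 0.6 points: 8.3%.

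Both tails, for other comparison-arm shares:

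| Comparison share | Intervention +10 points | Intervention +20 points |
|---|---|---|
| 50% | 9.7% | 22.9% |
| 60% | 8.3% | 17.6% |
| 70% | 7.4% | 14.4% |
| 80% | 6.9% | 12.2% |

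**5. Which adjustment works.** Simulated trials had 50 ACPs per arm, 5 patients each, ICC 0.07, no treatment effect and 60% exposed in the comparison arm. The figures below are from 500 runs per scenario, using a logistic GEE in place of the random-effect model.

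| Exposed in intervention arm | Unadjusted | Linear DBI term, all patients | DBI above 0 only, DBI as covariate |
|---|---|---|---|
| 60% | 4.0% | 5.2% | 4.6% |
| 70% | 8.0% | 6.8% | 6.4% |
| 80% | 18.2% | 7.8% | 3.8% |
| 90% | 36.8% | 12.8% | 5.6% |

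Monte Carlo error is about 1 point near 5%, and about 2 points at the largest rates. A 4,000-run beta-binomial simulation gave 8.1% and 18.6% unadjusted at 70% and 80%, and 4.8% in both among the exposed. A third simulation gave about 9% and 19% unadjusted, and about 6.5% and 10% with continuous DBI. A linear term removes only part of the bias, because the step between DBI 0 and DBI above 0 is not linear on the logit scale.

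**6. Power.** Suppose the shares are balanced and only exposed patients are analysed, keeping the design effect at 1.28. Power is then 86.8%, 84.3%, 82.5%, 81.1% and 80.1% for exposed shares of 50%, 60%, 70%, 80% and 90%, against 79.3% unadjusted. Across the formula and simulations, the gain from adjustment was about 0 to 8 points.

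**The case against.** **Adjustment is already planned, and an unadjusted primary analysis is common.** True. At 80% v 60% with 250 per arm the imbalance has z = 0.20/√(2·0.7·0.3/250) = 4.9, and at 70% v 60% z = 2.3 (both ignoring clustering), so the imbalance rule might well bring DBI in. But the primary result would stay biased, and the rule would decide the model after the data were seen. The article fixes these model terms itself, so this is not a detail left to an analysis plan that is not shown.

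**Safeguards exist.** Patients are recruited in order of referral and receive a standardised invitation. These limit selection. Each ACP still screens and invites, knowing the arm, and the Limitations section still regards the risk as live.

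**Limitations does not mention DBI.** Correct. A reader might infer that it predicts enrolment of patients with high DBI. It says only that patients who may benefit could be favoured. Exposure to DBI medicines is one plausible route. Willingness to deprescribe is another, and no DBI term removes it.

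**The size rests on assumptions.** This stands. Neither the exposed share nor any imbalance is documented.

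**Power.** A reader might infer that the trial is underpowered because some patients cannot respond. The documents do not support this: the 20% and 10% are proportions of all participants, so patients at DBI 0 are already within those rates, and 80% power reproduces.

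**Conclusion.** The point holds as a weakness in the primary analysis. The mechanism follows from the text: certain non-responders are eligible, recruitment is unblinded and follows allocation, and the primary model ignores the variable that separates those who can respond from those who cannot. With no treatment effect and an assumed 60% exposed in the comparison arm, the false-positive rate is about 8–9% if the intervention arm has 70% exposed, and about 18–19% if it has 80%. With equal shares there is no bias of this kind.

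It would go too far to say that the trial will be biased, that baseline adjustment is absent, or that the power statement is wrong. The case rests on bias; the efficiency gain is a modest extra.

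**What to change.** Prespecify the primary mixed logistic model, with arm and the ACP random effect, in one of two forms:

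1. Primary analysis set: patients with baseline DBI above 0, with continuous baseline DBI as covariate.
2. All patients, with an indicator for baseline DBI above 0 plus continuous DBI.

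The first is easier to fit. In the second, no patient at DBI 0 can have the event, so the indicator has no finite maximum-likelihood estimate and the arm effect comes from the exposed patients anyway. In a fixed-effects logistic fit to one simulated data set, both forms gave the same arm estimate and standard error. Whichever form is used, say that the effect applies to exposed patients. An all-patient difference follows by multiplying by one common exposed share: at 60%, 33.3% v 16.7% among the exposed is 20% v 10% overall.

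Also:
- drop the choice of covariates by observed imbalance and name any others in advance;
- report the share with DBI 0 by arm;
- keep the unadjusted model as a supporting analysis;
- state that selection on willingness to deprescribe would remain.

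The cost is wording only. Baseline DBI is already collected in both arms before the intervention report is produced, so no visits, data or patients are added. The change should be fixed before outcome data are seen by arm.

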Comorbidity and Physical Function			
Comorbidities	FCI	✓	✓
Cognition	Mini-Cog© [46]	✓	✓
Independent activities of daily living	NHCCSFSI	✓	✓
Physical Function	SPPB	✓	✓
Falls History		✓	✓
Others			
Institutionalisation (e.g. hospitalisation)		✓	✓
Physician visits (e.g. GP or specialist appointments)			✓
Mortality			✓
Goals of care^b^		✓	

^a^at the time of the HMR interview; ^b^only for patients in the intervention arm of the study

*PhARIA* The Pharmacy Access/Remoteness Index of Australia – quantifies degree of remoteness (geographic and professional) [47], *OTC* Over-the-counter, *PRN* when required, *MGL* Morisky, Green, Levine Scale [48], *rPATD* revised Patients’ Attitudes Towards Deprescribing [34], *rPATDCog* Revised Patients’ Attitudes Towards Deprescribing for people with Cognitive impairment [35], *DBI* Drug Burden Index [28], *FCI* Functional Comorbidities Index [49], *NHCCSFSI* National Home and Community Care Services Functional Screening Instrument [50], *SPPB* Short Physical Performance Battery [51], *GP* General practitioner

↑↓ = changes

The Morisky Green Levine Scale will be used to measure self-reported patient medication adherence [48]. Cognitive impairment will be assessed using the Mini-Cog© [46, 52–54]. The National Home and Community Care services Functional Screening Instrument (NHCCSFSI) (part one) and the Short Physical Performance Battery (SPPB) will be used to assess the functional status of patient participants [50, 51]. Details regarding scoring of these measures used in this study can be found in Additional file 1.

Data to calculate the Functional Comorbidity Index (FCI) will be collected from the patients. The FCI is a sum of 18 self-reported comorbid conditions with a score of 0–18. The FCI will also be used to measure comorbidities that predict physical function in older adults. A higher FCI score indicates greater morbidity and is associated with poorer physical function [49].

Falls (any fall in the last 12 months at baseline and number of falls at 3-months), institutionalisation (admission to hospital in the last 12 months at baseline and number of days admitted to hospital, nursing home or respite care at 3-months) and the number of physician visits (GP and specialist) will be captured over 3 months by providing patients and/or their carers a calendar to self-record events that will be collected by ACPs.

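### For secondary clinical outcomes measured at both visits, the outcome's own baseline should be in the main model, not in a conditional secondary analysis: a modest, nearly free gain in precision

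*Protocol article*

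**What the plan says.** The Statistical analyses section assigns model families by outcome type: "Binary continuous and count outcomes will be analysed using logistic, linear and negative binomial regression models, respectively". It then fixes their content: "All models will include a covariate for the intervention group, with a random effect for the clusters (ACPs"). No baseline term is named there.

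Baseline adjustment comes later in the section, in the list of secondary analyses: "Where appropriate, to conduct further adjusted analyses, covariates will be included for the patients’ baseline value (for that outcome"). The same item adds "any baseline characteristic for which there is evidence of imbalance between intervention and comparison groups".

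The data are already collected. Outcomes and follow-up states: "All ACPs will be required to collect additional information of their HMR recipients at baseline (during HMR interview) and at a 3-month follow-up visit". Table 1 ticks both visits for MGL adherence, Mini-Cog, NHCCSFSI and SPPB. Falls differ, because the two visits record different things: "any fall in the last 12 months at baseline and number of falls at 3-months".

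The Limitations section says of the trial: "It is not powered to assess differences in clinical outcomes, such as physical and cognitive function, even though this data will be captured".

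**The concern.** A patient's score at baseline is usually the strongest single predictor of the same score three months later. A model without it leaves that predictable variation in the residual, so the confidence interval for the arm difference is wider than it need be. The loss falls on outcomes that serve the second aim and half of the hypothesis, and that the article says the trial could not be powered for.

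The second issue is baseline imbalance. Pharmacists are randomised first, then recruit their own patients knowing their arm, and the Limitations section foresees that intervention pharmacists may favour certain patients. A main model without the baseline makes no allowance for a measured difference at the start. The analysis that would do so is optional and is bundled with covariates chosen after looking at the data.

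**Working it through.** **The plan's own figure.** The stated size (500 patients, 80% power, 20% against 10%, two-sided 5%, ICC 0.07) concerns the primary binary outcome. It needs 199 per arm before clustering. The design effect is 1 + (5 − 1) × 0.07 = 1.28, so the total is 2 × 199 × 1.28, or 510 after rounding up per arm. Power at 250 per arm is 79.3%. The figure reproduces, and this point does not touch it.

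**Inputs for the secondary outcomes.**
- From Sample size: 500 patients, equal arms, 5 per pharmacist.
- ICC 0.07: given for DBI and assumed here for the clinical outcomes.
- Assumed, because the article gives neither: the baseline to 3-month correlation rho (0.3, 0.5, 0.7) and a standardised difference d = 0.20.
- The outcome is analysed as continuous.

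**Formulas.** Effective patients per arm: 250 / 1.28 = 195.3. In SD units the standard error of the arm difference is sqrt(2v / 195.3), and power = Phi(d / SE − 1.96), where
- v = 1 for the raw 3-month value,
- v = 2(1 − rho) for a change score,
- v = 1 − rho² for the 3-month value adjusted for baseline.

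Both unadjusted forms are shown because the article calls these outcomes changes but does not say which quantity is modelled. With v = 1 the SE is sqrt(2 / 195.3) = 0.101, and power is Phi(0.20 / 0.1012 − 1.96) = 50.7%.

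| rho | Power, 3-month value | Power, change score | Power, adjusted | Variance cut vs 3-month value | Variance cut vs change score |
|---|---|---|---|---|---|
| 0.3 | 50.7% | 38.6% | 54.5% | 9% | 35% |
| 0.5 | 50.7% | 50.7% | 62.6% | 25% | 25% |
| 0.7 | 50.7% | 72.3% | 79.0% | 49% | 15% |

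The variance cuts are rho² against the 3-month value and 1 − (1 + rho)/2 against the change score.

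The difference detectable with 80% power is 2.80 × SE. It is 0.284 SD for the 3-month value, and 0.270, 0.246 or 0.202 SD after adjustment.

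**Simulation check.** I used 4,000 simulated trials per rho, with 100 clusters of 5, ICC 0.07 and least squares with the baseline added. The ratios of adjusted to unadjusted SE were 0.947, 0.871 and 0.716. The formula sqrt(1 − rho²) gives 0.954, 0.866 and 0.714.

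**Chance imbalance.** In the same simulations the baseline difference between arms varied by chance with an SD of about 0.10. The unadjusted 3-month estimate correlated with that difference at 0.32, 0.49 and 0.70. The adjusted estimate correlated at about zero. A chance gap of 0.2 SD with rho = 0.5 moves the raw 3-month contrast by 0.5 × 0.2 = 0.1 SD. It moves the change score by −(1 − 0.5) × 0.2 = −0.1 SD.

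**The case against.** **Adjustment is already planned.** The dispute is only over which of two planned analyses is called main, and the conditional wording may just mean wherever a baseline exists, since Table 1 has none for physician visits or mortality. This is fair, and it is why the point is modest. The section still places the adjusted model among the secondary analyses, so the main estimate is the less precise one.

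**The gain covers few outcomes and rests on assumptions.** This stands. The formulas hold only for outcomes analysed as continuous. Scoring is in an additional file not shown, so NHCCSFSI, Mini-Cog and MGL count only if scored that way. In a logistic model, adjustment does not narrow the SE of the log odds ratio, although power can rise. The falls baseline is not the same measure as the falls outcome. The gain is small at some values: about 4 points at rho 0.3 against the 3-month value, and under 5 points against a change score once rho is about 0.8 or more.

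**Stronger readings that the article does not support.**
- A reader might infer that the unadjusted estimates are biased by selective recruitment and that adjustment cures this. Under chance imbalance alone, the unadjusted estimate is unbiased over repeated randomisations. If recruitment brings in stably different populations, a change score need not be biased. Adjustment handles only the measured part of the gap.
- A reader might infer that nothing says which estimate carries the conclusion. The article's separation of main from secondary analyses does say it.

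**Conclusion.** The point holds as an efficiency improvement of modest size. It is not an error or a contradiction, and it leaves the primary DBI outcome alone. For a clinical outcome analysed as continuous, adding its baseline reduces variance at every correlation examined. For a 0.20 SD difference the gain is 4 to 28 points of power against the raw 3-month value (rho 0.3 to 0.7), and 16 down to 7 points against a change score. It also removes the effect of chance baseline imbalance and the measured part of any recruitment imbalance, but not unmeasured selection.

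The size rests on rho, d and the ICC for the clinical outcomes, none of which the article gives. The direction does not depend on them. If an analysis plan not shown here already puts the baseline in the main model, the article's wording only needs to be aligned with it.

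**What to change.** In Statistical analyses, state that for each secondary outcome with a like-for-like baseline (SPPB, NHCCSFSI, Mini-Cog, MGL) the main model analyses the 3-month value with intervention group, that outcome's baseline value and a random effect for pharmacist. Keep the model with arm and pharmacist only as a sensitivity analysis. Delete the baseline value from the conditional item in the secondary list. Any fall in the 12 months before baseline may be added to the falls model, described as a prognostic covariate.

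The cost is a wording change before unblinding, with no new data or patients. There are two downsides. The handling of missing baseline scores must be specified. For any outcome analysed as binary, the odds ratio becomes conditional on baseline and should be reported as such.
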